## Abstract

**Background:**

The treatment of eating disorders is a difficult endeavor, with only a relatively small proportion of clients responding to and completing standard cognitive behavioural therapy (CBT). Given the prevalence of co-morbidity and complex personality traits in this population, Schema Therapy has been identified as a potentially viable treatment option. A case series of Group Schema Therapy for Eating Disorders (ST-E-g) yielded positive findings and the study protocol outlined in this article aims to extend upon these preliminary findings to evaluate group Schema Therapy for eating disorders in a larger sample (*n* = 40).

**Methods/design:**

Participants undergo a two-hour assessment where they complete a number of standard questionnaires and their diagnostic status is ascertained using the Eating Disorder Examination. Participants then commence treatment, which consists of 25 weekly group sessions lasting for 1.5 h and four individual sessions. Each group consists of five to eight participants and is facilitated by two therapists, at least one of who is a registered psychologist trained on schema therapy. The primary outcome in this study is eating disorder symptom severity. Secondary outcomes include: cognitive schemas, self-objectification, general quality of life, self-compassion, schema mode presentations, and Personality Disorder features. Participants complete psychological measures and questionnaires at pre, post, six-month and 1-year follow-up.

**Discussion:**

This study will expand upon preliminary research into the efficacy of group Schema Therapy for individuals with eating disorders. If group Schema Therapy is shown to reduce eating disorder symptoms, it will hold considerable promise as an intervention option for a group of disorders that is typically difficult to treat.

**Trial registration:**

ACTRN12615001323516. Registered: 2/12/2015 (retrospectively registered, still recruiting).

## Background

The treatment of eating disorders is a difficult endeavor, with only a relatively small proportion of clients responding to standard cognitive behavioural therapy (CBT). Less than half of those with bulimia nervosa (BN) have recovered at follow-up after receiving CBT [17, 18, 23] and research supporting cognitive-behavioural treatment for anorexia nervosa (AN) is limited, with no clear indication of improvement in this population [6, 8]. Approximately 50% of patients with eating disorders continue to be highly symptomatic at 60-week follow-up following transdiagnostic CBT [16]. Further, treatment dropout rates are high amongst individuals with eating disorders [9, 43] with one literature review reporting an average drop-out rate of between 20 and 51% in inpatient settings and between 29 and 73% in outpatient settings [20].

The treatment of eating disorders is especially complicated by a high level of co-morbidity [3]. Approximately 69% of individuals with eating disorders may meet DSM IV (APA, 1994) diagnostic criteria for a personality disorder and 93% of these clients may also have other co-morbidity including anxiety and substance use disorders. Eating disorders are also associated with the presence of rigid personality features, which increases clinical complexity and is associated with poorer treatment outcomes [22, 26, 46]. Eating disorders have also been linked to a range of trauma-related risk factors, including childhood abuse and neglect, which may also be mediated by personality disorder diagnoses [5]. Individuals with eating disorders also commonly experience complex and difficult-to-treat symptomatology including dissociation, perfectionism, compulsive pathology, rigid thinking patterns [28, 30, 38, 49] and high levels of shame [7].

Given the prevalence of co-morbidity and complex personality traits in this population, it is important to consider the deeper belief systems underlying eating disorder presentations. Schema Therapy ([53]/1999) is becoming an increasingly popular psychological model for working with individuals with complex mental health and personality difficulties. Schema Therapy combines aspects of cognitive, behavioral, experiential, interpersonal and psychoanalytic therapies into one integrative and unified model [1]. The schemas that are targeted in treatment are enduring and self-defeating patterns that typically begin early in life. These patterns consist of negative/dysfunctional thoughts and feelings which have been repeated and elaborated upon, and pose obstacles for accomplishing one’s goals and getting one’s needs met [40]. These schemas are perpetuated behaviorally through the coping styles of schema maintenance, schema avoidance, and schema compensation. The Schema therapy model of treatment is designed to help the person break these negative patterns of thinking, feeling and behaving and develop healthier alternatives to replace them [1].

The evidence for schema therapy for individuals with complex mental health difficulties is growing. This approach has been applied, in both individual and group forms, to a wide variety of clinical disorders, including, borderline personality disorder [19, 21] and chronic depression [11, 34, 41, 42]. A recent stringent systematic review found medium to large effect sizes for schema therapy in the treatment of a range of psychological conditions [35]. Attention has recently been given to the applicability of Schema Therapy to individuals with eating disorders (Pugh, 2015). Evidence suggests that maladaptive schemas are more strongly held by individuals with anorexia and bulimia nervosa compared to normal controls [30]. Preliminary data [33, 38] supports the notion that it is the schema processes that are engaged in an attempt to avoid intolerable emotional states associated with these schemas that in fact determine whether an individual will manifest restrictive or bulimic eating pathology. Whereas restrictive eating pathology may be a compulsive behavior developed to prevent schemas being triggered at all (schema compensation), bulimic pathology may function alongside other impulsive behaviors as a method of escaping schema-related affect once schemas have already been triggered (schema avoidance) [33, 38].

Schema therapy has been used in individuals with eating disorders in one preliminary study [44]. Simpson et al. examined the use of Group Schema Therapy for Eating Disorders (STE-g) in a case series of eight participants with chronic eating disorders and high levels of co-morbidity. Treatment was comprised of 20 sessions which included cognitive, experiential, and interpersonal strategies, with an emphasis on behavioral change. Clinically significant change was observed from pre-treatment to six-month follow-up for eating disorder severity (*d* = 1.70), global schema severity (*d* = 1.59), shame (*d* = 0.91), and anxiety (*d* = 1.53). Clinically significant change in eating disorder severity at follow-up was also shown for the majority of completers (six participants out of eight completed the full treatment program). Self-report feedback suggested that group factors may catalyze the change process in schema therapy by increasing perceptions of support and encouragement to take risks and try out new behaviors, whilst providing a de-stigmatizing and de-shaming therapeutic experience [44].

The present study aims to extend upon the preliminary findings of Simpson et al. [44] to evaluate Schema Therapy in a large eating disordered sample (*n* = 40), in terms of reduction of symptoms, and assess feasibility, acceptability and predictors of outcomes. We aim to conduct 6 groups of schema therapy in two locations: 1) University of South Australia in Adelaide Australia and 2) Western Sydney University in Sydney Australia. The study will examine whether Schema Therapy reduces eating disorder symptoms and improves psychological wellbeing and quality of life, both at post treatment and follow-up.

## Method

### Participants

Approximately 40 participants will be recruited into the study. All participants will be females aged 18 years and over, meeting *Diagnostic and Statistical Manual of Mental Disorders, 5th Edition* criteria for an eating disorder, following a transdiagnostic approach (Fairburn, et al., 2003). Participants are recruited via word of mouth, letters to clinicians and advertisements through *Facebook* as well as support organisations such as *The Butterfly Foundation.* Participants are provided with information about the study and, if they agree to participate, are required to give written consent. Full disclosure of the purpose of the study, the potential benefits and risks associated with participation, and the confidential nature of information obtained in the study is explained to participants.

### Inclusion/ exclusion criteria

Participants with active psychotic symptoms, high suicide risk or current crisis status (self-disclosed at baseline), a BMI of less than 14, intellectual disability, and those who are consuming large amounts of alcohol/drugs are excluded from the study. All participants must have a general practitioner involved in their care to monitor their physical health in order to participate in this research.

### Overall study design

This study will be an uncontrolled single group repeated measures design. Ethics approval was secured and participants provided informed consent to participate. Participants are first screened over the phone to ensure suitability for the group. If they agree to participate in the group, they then undergo a two-hour assessment where they complete a number of standard questionnaires and their diagnostic status is ascertained. Participants then commence treatment which consists of 25 weekly group sessions lasting for 1.5 h. Participants are also provided with four individual sessions that they can book with one of the therapists whenever they want. Each group consists of six to eight participants and is facilitated by two therapists, at least one of whom is a registered psychologist with training on schema therapy, and supervised by a schema therapist. Participants complete psychological measures and questionnaires at pre, post, 6 month and 1 year follow-up.

### Measures

This study utilises a battery of assessments conducted at baseline, mid-treatment, end-of-treatment, and six- and twelve-month follow-up points. These assessments are conducted by fully registered psychologists who have received specialized training in the administration of standardized eating disorder measures. Table 1. Provides a summary of these assessments.

**Table 1 Tab1:** Assessments conducted at different time points

Measure	Baseline	Weekly	Mid	Post	6 months	12 months
EDE	x			x		
EDE-Q	x	x (abbrev)	x	x	x	x
YSQ-SF	x		x	x	x	x
SMI	x		x	x	x	x
WHO-5	x		x	x	x	x
CORE-10	x		x	x	x	x
SCS-SF	x		x	x	x	x
SATAQ	x		x	x	x	x
MCMI-III	x			x		
BSL-23	x			x	x	x

*Notes: EDE = Eating Disorder Examination; EDE-Q = Eating Disorder Examination- Questionnaire; YSQ-SF = Young Schema Questionnaire, short form; SMI = Schema Mode Inventory; WHO-5 = World Health Organisation-Five Well-Being Index; CORE-10 = Clinical Outcomes in Routine Evaluation-Outcome Measure; SCS = Self-Compassion Scale*- *Short Form; SATAQ = Sociocultural Attitudes Towards Appearance Questionnaire; MCMI-III = Millon Clinical Multiaxial Inventory- III; BSL-23 = Borderline Symptoms List*

#### *Eating Disorder Examination* (EDE; [15])

The EDE is a structured, investigator-based interview that measures the severity of symptoms of eating disorders. The scale can be used to ascertain an individual’s eating disorder diagnosis, as is the purpose of the measure in the current study. The EDE has been shown to have excellent reliability when administered by trained examiners [12].

#### *Eating Disorder Examination- Self-Report Questionnaire Version* (EDE-Q; [14])

The EDE-Q is a 36-item self-report questionnaire for the assessment and diagnosis of eating disorders. The EDE-Q yields four subscale scores—Restraint, Eating Concern, Weight Concern, and Shape Concern—as well as a global score, which is an average of all four subscales. The EDE-Q has been shown to have good convergent validity [10, 14]. Acceptable internal consistency and test–retest reliability have also been demonstrated [32, 37].

#### *Young Schema Inventory- Short Form* (YSQ-SF; [52])

The YSQ-SF is a self-report measure used to assess 15 different maladaptive schemas (emotional deprivation, abandonment, mistrust/abuse, social alienation, defectiveness, incompetence, dependency, vulnerability to harm, enmeshment, subjugation of needs, self-sacrifice, emotional inhibition, unrelenting standards, entitlement, and insufficient self-control). The scale consists of 75 items rated from one (*completely untrue of me*) to six (*describes me perfectly*). The scale has been shown to have good psychometric properties [25, 50].

#### *Schema Mode Inventory-Short Form* (SMI; [31])

The SMI measures the presence of 14 schemas modes: Vulnerable Child, Angry Child, Enraged Child, Impulsive Child, Undisciplined Child, Happy Child, Compliant Surrender, Detached Protector, Detached Self-Soother, Self-Aggrandizer, Bully and Attack, Punitive Parent, Demanding Parent and Healthy Adult modes. The questionnaire consists of 118 items which are given frequency ratings using a Likert scale ranging from one (never or hardly ever) to six (always). An overall score is calculated from the scale sum score divided by the number of items in that scale. The short form of the SMI has been shown to have acceptable internal consistencies amongst the 14 subscales (Cronbach α’s from .79 to .96) as well as adequate test-retest reliability and moderate construct validity [31].

#### *World Health Organisation-Five Well-Being Index* (WHO-5; [51])

The WHO-5 is an assessment of general wellbeing consisting of five statements (e.g. *I have felt cheerful and in good spirits* and *I have felt calm and relaxed*), which participants rate on a six-point scale (from *never* to *always*), with a possible total score varying from 0 to 25. Higher scores on the WHO-5 reflect better well-being.

#### *Clinical Outcomes in Routine Evaluation-Outcome Measure* (CORE-10; [2])

The CORE-10 is a self-report measure of general psychological distress. The CORE-10 includes 10-items which the respondent rates on a five-point Likert scale (from *not at all* to *most or all of the time*), for example *I have felt tense, anxious or nervous* and *I have felt panic or terror*. The CORE-10 has been shown to have good internal reliability (α = .90) and a correlation of.94 with the CORE-OM [2].

#### *Self-Compassion Scale*- *Short Form* (SCS-SF; [39])

The SCS-SF is a 12-item, self-report scale which assesses the positive and negative aspects of the three main components of self-compassion: Self-Kindness (e.g., *When I’m going through a very hard time, I give myself the caring and tenderness I need*) versus Self-Judgment (e.g., *I’m disapproving and judgmental about my own flaws and inadequacies*); Common Humanity (e.g., *When I feel inadequate in some way, I try to remind myself that feelings of inadequacy are shared by most people*) versus Isolation (e.g., *When I fail at something that’s important to me, I tend to feel alone in my failure*); and Mindfulness (*When something upsets me I try to keep my emotions in balance*) versus Over-Identification (*When I’m feeling down I tend to obsess and fixate on everything that’s wrong).* Responses are given on a five-point scale ranging from one (*almost never*) to five (*almost always*). A total self-compassion score is calculated as a mean of all items and higher scores correspond to higher levels of self-compassion. The SCS-SF has good psychometric properties, with high internal consistency (α = .85; [45]) and a very high correlation with the long form of the SCS [39].

#### *Sociocultural Attitudes Towards Appearance Questionnaire- Internalization subscale* (SATAQ; [24])

The SATAQ is a 14-item inventory assesses women’s recognition and acceptance of societally prescribed standards of physical appearance, particularly the thin ideal. The 8-item Internalization subscale is used in the present study and measures the extent to which the individual personally accepts these standards. Statements such as *I tend to compare my body to people in magazines and on TV* are rated from one (*completely disagree*) to five (*completely agree*). The SATAQ converges satisfactorily with other measures of body image and eating disturbance [24, 47].

#### *Millon Clinical Multiaxial Inventory- III* [36]

The MCMI-III is a psychological assessment that provides information on longstanding personality patterns and clinical symptomatology. The tool consists of 175 items that are scored on a *True/False* basis that are scored to produce 28 clinical subscales. Reliability and validity studies on the MCMI indicate that is generally a psychometrically sound instrument. The scale demonstrates good internal consistency with alpha coefficients of above.80 for the majority of the scales (manual). Test-retest reliability has been shown to be moderate to high [13, 29].

#### *Borderline Symptoms List* (BSL-23; [4])

The BSL-23 is a questionnaire used to assess the degree of symptoms of BPD, such as poor self-esteem, dysphoric emotions, suicidal intention and impulsive behaviors. The scale consists of 23 items (for example: *I experienced stressful inner tension* and *I wanted to punish myself*) rated on a five-point Likert scale from 0 (*not at* all) to 4 (*very strong*). A total score is obtained by summing responses and higher scores represent more severe BPD symptomatology. The BSL-23 has good psychometric properties with high internal consistency (α = 0.94–0.97) and the ability to discriminate personality disorder patients from patients with other clinical symptomatology (mean effect size of 1.13; [4]).

### Primary outcomes

Eating disorder symptom severity is the primary outcome of this, as measured by the EDE and EDE-Q. The EDE will be used for pre to post, but due to limited resources only the EDE-Q will be completed at follow-up.

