### Data analysis

Within-patient standardized effect size information (i.e., Cohen’s d) from baseline to end-of-treatment, and from baseline to follow-up will be calculated for eating psychopathology, and all secondary outcomes. Clinical outcome data will be analysed using intention to treat criteria. Data from outcome measures will be analysed with paired sample T-test. To assess group differences between the two treatment sites, independent t-tests will be used. The effect size of outcome measures will be compared to the effect size reported for previous studies CBT for eating disorders. The criterion used for statistical significance will be *p* < 0.05. Sample size was estimated assuming 80% power, significance level at 0.05, and an effect size of 0.5; 26 people are needed. Assuming a 50% drop out as documented in previous CBT trials, we will need around 40 people.

At the completion of the treatment, a random set of participants will be invited to provide qualitative feedback on their experiences of the group treatment. These interviews will be one-to-one, and conducted either face-to-face, or via telephone, and are expected to last for between 30 and 60 min. Transcripts of these interviews will be made and the data will be analysed using a thematic analyses approach. This information will be used to provide preliminary information about treatment efficacy and acceptability, and inform the design of future studies.

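### The primary outcome is measured by two unranked instruments and tested at more than one time point at p < 0.05, and the stated purpose of one instrument conflicts with its primary role

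*Protocol article*

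**What the plan says.** All references are to the protocol article.

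- **Primary outcomes:** "Eating disorder symptom severity is the primary outcome of this, as measured by the EDE and EDE-Q". The section then divides the schedule: "The EDE will be used for pre to post, but due to limited resources only the EDE-Q will be completed at follow-up".
- **Measures, Table 1:** the EDE is taken at baseline and post. The EDE-Q is taken at baseline, mid-treatment, post, 6 months and 12 months, with an abbreviated form weekly.
- **Measures, EDE description:** after noting that the interview can establish an eating disorder diagnosis, it adds "as is the purpose of the measure in the current study".
- **Measures, EDE-Q description:** four subscales and a global score. No section says which of these is the primary score.
- **Data analysis:** effect sizes "from baseline to end-of-treatment, and from baseline to follow-up will be calculated for eating psychopathology, and all secondary outcomes". On testing: "Data from outcome measures will be analysed with paired sample T-test". The significance criterion is p < 0.05. The sample size rests on 80% power, a 0.05 significance level and an effect size of 0.5, giving 26 people, raised to around 40 for dropout. The calculation names no instrument, score or time point.

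**The concern.** A primary outcome should lead to one pre-specified result, or to a stated rule for combining several. Here there are two instruments and up to three post-baseline time points. Nothing says which comes first, whether both must succeed, or how the 0.05 is shared. A significant change on either instrument at any of these times could be reported as a positive primary result, so the true error rate exceeds the stated 5%.

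The two statements about the EDE add to this. If its purpose is diagnosis, its post-treatment score is a diagnostic check. If it measures the primary outcome, that score is a main result. A reader cannot tell which.

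The choice also matters because the Data analysis section intends to compare this study's effect size with those from earlier CBT studies. Which instrument and visit supply that effect size is left open.

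**Working it through.** **Step 1. The plan's own sample size.** Inputs from Data analysis: d = 0.5, 80% power, alpha 0.05, paired t-test. Sidedness is not stated.

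- Normal approximation, n = ((z_alpha + z_0.80)/d)². One-sided: ((1.645 + 0.842)/0.5)² = 24.7, so 25. Two-sided: ((1.960 + 0.842)/0.5)² = 31.4, so 32.
- Exact noncentral t: 27 one-sided, 34 two-sided.
- Power at n = 26: 79.8% one-sided, 68.8% two-sided.

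The figure of 26 is therefore reproduced, to within one or two people, as **one** one-sided test at 0.05. It makes no allowance for a second primary test.

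**Step 2. Counting the primary tests.** Instruments come from Primary outcomes, visits from Table 1 and contrasts from Data analysis.

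| Contrast from baseline | EDE | EDE-Q |
|---|---|---|
| End of treatment | yes | yes, if counted |
| 6 months | not collected | yes |
| 12 months | not collected | yes |

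If Primary outcomes means the EDE for pre to post and the EDE-Q for follow-up, there are three tests. If both instruments count wherever they are collected, there are four. Mid-treatment is left out because Data analysis plans no contrast there. Subscales are left out because no test of them is stated.

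**Step 3. Chance of at least one false positive, each test at 0.05.** If independent, 1 − 0.95^k:

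- k = 3: 1 − 0.95³ = 0.143
- k = 4: 1 − 0.95⁴ = 0.185

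The tests share participants and a construct, so they will be correlated. The document gives no correlation, so a range is assumed. Simulation with four equally correlated normal statistics (one million draws) gives:

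| Assumed correlation | Two-sided 0.05 | One-sided 0.05 |
|---|---|---|
| 0.5 | 15.6% | 14.4% |
| 0.7 | 13.1% | 12.1% |
| 0.8 | 11.4% | 10.5% |
| 0.9 | 9.4% | 8.8% |

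Every entry exceeds 5%.

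**Step 4. What keeping all four as primary would cost.** With Bonferroni, 0.05/4 = 0.0125 per test. The required n for d = 0.5 is then 41 one-sided or 48 two-sided, and power at n = 26 falls to 57% or 46%. One named primary avoids this and matches the single-test calculation in step 1.

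**Step 5. The two statements on the EDE.** The EDE description gives diagnosis as its purpose in this study. Primary outcomes uses it from pre to post as a measure of symptom severity. Both cannot stand as worded.

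**The case against.** **Context.** The study is a single-group, uncontrolled proof of concept. Its analysis section opens with effect sizes, and multiplicity rules are commonly left to an analysis plan, which is not shown here. This tempers the importance of the error rate. It does not remove the point, because the article itself states two primary measures, a single unadjusted criterion and conflicting purposes for the EDE. Those are statements, not omissions.

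**Size.** Sidedness is not stated, and only false claims of benefit may matter. If the tests are two-sided, the chance of at least one false benefit among four is 1 − 0.975⁴ = 9.6% if independent, and 6.5% or 5.7% at assumed correlations of 0.7 or 0.8. That is fair. The figures are smaller, but they should be set against 2.5% for a single two-sided test in the direction of benefit, so the inflation remains.

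**Change of instrument.** A reader might infer from "due to limited resources only the EDE-Q will be completed at follow-up" that the pre-post effect is on the interview and the follow-up effect on self-report, so that an apparent gain or relapse after treatment could be an artefact. The document does not support this. Table 1 collects the EDE-Q at baseline, post, 6 and 12 months, and Data analysis plans contrasts from baseline only. No comparison of a post-treatment EDE with a follow-up EDE-Q is stated.

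**Diagnosis alone.** A reader might also infer that the EDE is restricted to diagnosis. The description does not say so. It also says that the interview measures symptom severity, and Table 1 repeats it at post. The conflict is one clause against another section: real, but narrow.

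**Wider test counts.** Multiplying every instrument and subscale by every visit gives much larger totals. Those are not planned primary tests and do not bear on this point.

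**Conclusion.** The concern holds in this form: two unranked primary instruments, no primary score or time point, and a flat 0.05 criterion give three to four primary tests where the sample size assumes one. The chance of at least one false-positive primary result is 14% to 19% under independence. For four tests it is about 9% to 16%, two-sided, at correlations of 0.5 to 0.9. The correlations and the sidedness are assumptions, but the direction does not depend on them. The EDE description and the Primary outcomes section also disagree on what the EDE is for.

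The point is worth correcting but does not undermine the data. The measurements needed for a single clear primary are already scheduled, and same-instrument comparisons are available throughout on the EDE-Q.

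**What to change.** 1. In Primary outcomes, name one instrument, one score and one time point. An example is the EDE-Q global score, change from baseline to end of treatment, since Table 1 collects the EDE-Q at every assessment. The EDE at end of treatment is a defensible alternative, and the documents do not compel either.
2. Make the other instrument and the 6- and 12-month contrasts secondary.
3. Reword the EDE description or Primary outcomes so that they agree on the role of the EDE.
4. State in Data analysis that the sample size refers to that one primary, and whether the test is one- or two-sided.
5. Record the date of the choice and that it was made without sight of outcome data. The Discussion reports four groups completed and two more begun, so an undated choice now would carry the selection risk that it is meant to remove.

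**Cost:** no new data or visits. The change is one of wording, plus a dated record of who had access to outcome data. The downside is that one of the two instruments is no longer primary.
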